## Abstract

**Background:**

Postoperative delirium (POD) is a common complication following cardiac surgery and increases postoperative morbidity and mortality. Intraoperative electroencephalogram (EEG) burst suppression suggests excessively deep anesthesia and predicts POD. Use of remimazolam provides a stable hemodynamic status and an appropriate depth of anesthesia. We aim to assess remimazolam administered for anesthesia and sedation in elderly patients having cardiac surgery.

**Methods:**

This is a randomized controlled clinical trial with noninferiority design. A total of 260 elderly patients aged equal to or greater than 60 years undergoing cardiac surgery will be randomly allocated to receive remimazolam or propofol (1:1) for general anesthesia and postoperative sedation until extubation. The primary outcome is the cumulative time with EEG burst suppression which is obtained from the SedLine system. The noninferiority margin is 2.0 min. The secondary outcomes include the POD occurrence within the first 5 days postoperatively and the duration of perioperative hypotension.

**Discussion:**

This noninferiority trial is the first to evaluate the effect of perioperative remimazolam administration on EEG burst suppression, POD occurrence, and duration of hypotension in elderly patients who undergo cardiac surgery.

**Trial registration:**

Chinese Clinical Trial Registry (ChiCTR2200056353).

## Introduction

1

Postoperative delirium (POD) is a common complication following surgery with the characteristics of acute dysfunction in attention and awareness [1]. Patients with POD have an increased risk for prolonged hospitalization, dementia, and mortality [2]. The predisposing and precipitating factors of POD include advanced age, electroencephalogram (EEG) burst suppression, cardiac surgery, and admission to intensive care unit (ICU) [[3], [4], [5]]. Patients having cardiac surgery show a high incidence of POD ranging from 10 % to 50 %, and its prevention and treatment remain challenging [6,7].

The indices calculated by EEG monitors such as bispectral index have become widely used to assess the depth of anesthesia and sedation; however, these indices characterize only partial raw EEG features [[8], [9], [10]]. In the recent years, multimodal brain monitoring has been applied to provide individualized anesthesia, illustrating real-time EEG waveforms and derived parameters (density spectral array, spectral edge frequency [SEF], patient state index [PSI], electromyography, and suppression ratio) [11]. Recent studies showed that the utilization of EEG monitoring detected burst suppression and may improve perioperative neurocognitive function [12,13].

Remimazolam is an ultra-short γ-aminobutyric acid type receptor agonist that provides sedation with quick onset and rapid metabolism [14]. The use of remimazolam led to safe and effective sedation for endoscopic procedures [[15], [16], [17], [18]]. Regarding its efficacy for general anesthesia, remimazolam was not inferior to propofol [19]. For patients undergoing cardiovascular surgery, remimazolam reduced cardiac depression and adverse events compared with propofol or etomidate [[20], [21], [22], [23]].

We design this randomized controlled noninferiority trial on remimazolam anesthesia in elderly patients undergoing cardiac surgery. We hypothesize that anesthesia and sedation using remimazolam would be noninferior to propofol in terms of EEG burst suppression. In addition, we will assess the POD occurrence and hypotension duration in these patients.

## Methods

2

### Study design

2.1

This randomized controlled noninferiority trial is conducted at the First Affiliated Hospital of Soochow University. A total of 260 elderly patients who are scheduled for cardiac surgery will be recruited. After the Medical Ethics Committee approved this trial (No. 2021–303), we completed the registration at the Chinese Clinical Trial Registry (identiﬁer: ChiCTR2200056353). We plan to recruit all patients by the end of December 2024. Written informed consent will be obtained. We report this trial protocol in accordance to the Standard Protocol Items: Recommendations for Interventional Trials (SPIRIT) guideline [24]. Table 1 presents the scheduled process of enrollment, interventions, and measurements. Fig. 1 shows the flowchart of patients in this trial.

**Table 1 tbl1:** Schedule of patient enrollment, study interventions, and measurements complying with the SPIRIT statement.

Timepoint	Study Period					
	Enrollment	Allocation	Post-allocation			Close-out
	*Pre-anesthesia visit*	Before surgery	During surgery	postoperative day 1 to 5	Hospital discharge	Postoperative day 30
**Enrollment**						
Inclusion criteria	**×**					
Exclusion criteria	**×**					
Written informed consent	**×**					
Randomization		**×**				
Allocation		**×**				
**Interventions**						
Remimazolam			**×**	**×** (until extubation)		
Propofol			×	× (until extubation)		
**Measurements**						
Electroencephalogram data			**×**			
Intraoperative awareness			**×**			
Duration of hypotension			**×**	**×**		
Use of vasopressors/inotropes			**×**	**×** **×**		
Postoperative delirium				**×** **×**		
PONV				**×**		
Postoperative complications					**×**	
Reoperation				**×**	**×**	
Mechanical ventilation					**×**	
Length of ICU stays					**×**	
Length of hospital stays					**×**	
30-day readmission						**×**
30-day mortality						**×**

According to SPIRIT statement of defining standard protocol items for clinical trials.

PONV, postoperative nausea and vomiting.

**Fig. 1 fig1:**
[figure not shown]
Study flow diagram.

### Eligibility criteria

2.2

The inclusion criteria are (1) aged equal to or greater than 60 years, (2) American Society of Anesthesiologists (ASA) classification I to IV, (3) planned to have elective cardiac surgery, and (4) with planned ICU admission. The cardiac procedures include coronary artery bypass grafting and/or valve surgery under cardiopulmonary bypass (CPB).

Exclusion criteria are (1) allergy to study medications, (2) surgical procedures involving aortic arch, (3) use of deep hypothermic circulatory arrest or low flow; (4) preoperative left ventricular ejection fraction <30 %, (5) severe hepatic dysfunction (Child-Pugh class C) or renal replacement therapy, (6) severe chronic respiratory disease, (7) history of mental diseases or taking antipsychotic medications, (8) Mini-Mental State Examination (MMSE) score ≤23, or (9) declined to provide informed consent.

### Randomization and blinding

2.3

A research assistant not involved in the other parts of the trial generates the random sequence with the use of online randomization (https://www.91trial.com; 1:1, permuted blocks of size 2 or 4). Allocation concealment will be protected by password. According to the randomization results, another research stuff assigns patients into one of the two study groups (the remimazolam group and the propofol group). As remimazolam and propofol have different appearances, the perioperative care team will not be blinded to the study groups; however, they are unaware of the study hypothesis. All patients, data collectors, outcome assessors, and a statistician will be masked to the assignment.

### Anesthesia

2.4

Patients will receive an ASA routine monitoring. Hemodynamic status will be monitored using the FloTrac/Vigileo (Edwards Lifesciences, CA) via radial artery cannulation. Multimodal brain monitoring with the SedLine® (Masimo, CA) system will be applied to monitor intraoperative EEG continuously. Attending anesthesiologists will receive full education of the characteristic EEG patterns in the SedLine system during propofol and remimazolam anesthesia.

To induce general anesthesia, patients will be administered with intravenous sufentanil 0.5 μg/kg and one of the study medications (remimazolam or propofol, with details described below). Rocuronium 0.8 mg/kg will be given for endotracheal intubation. To maintain anesthesia, patients will receive an infusion of remimazolam or propofol, titrated to an appropriate depth of anesthesia. Intermittent sufentanil 0.1 μg/kg will be given to achieve intraoperative analgesia, and rocuronium 0.1 mg/kg will be administered for neuromuscular block. Patients will receive intraoperative mechanical ventilation (tidal volume 6–8 ml/kg, 12–18 breaths per minute, 50–80 % of oxygen in air) and a standardized normothermic CPB (a continuous nonpulsatile perfusion of 2–2.4 l/min/m^2^). Patients will receive erythrocyte transfusion when hematocrit is ≤ 21 % on CPB and ≤24 % off CPB. Vasoactive and inotropic drugs (phenylephrine, epinephrine, norepinephrine, nitroglycerine, or dobutamine) will be used at the discretion of attending anesthesiologists. To provide prophylaxis of nausea and vomiting, intravenous dexamethasone 5 mg and palonosetron 0.075 mg will be given. Upon the completion of surgery, patients will be admitted to a designated cardiac ICU and receive sedation with a continuous infusion of the study medications until extubation.

### Study interventions

2.5

Fig. 2 illustrates the details of study interventions. Patients in the remimazolam group will receive intravenous remimazolam 0.2–0.3 mg/kg to induce anesthesia, an infusion at 0.6–2 mg/kg/h to maintain anesthesia, and 0.2–1 mg/kg/h for sedation until extubation in the ICU. Patients in the propofol group will receive intravenous propofol 1.0–1.5 mg/kg for anesthesia induction, an infusion at 3–10 mg/kg/h during surgery, and sedation with 1–5 mg/kg/h until extubation. The infusion rate of study medications in both groups will be adjusted according to the observation of EEG information. The primary target is to minimize EEG burst suppression episodes by decreasing propofol or remimazolam administration. The secondary targets are to maintain left and right SEF values of 8–15 and PSI values of 25–50 [25]. Other intravenous hypnotic agents (such as midazolam, etomidate, dexmedetomidine, or ketamine) or inhalational agents (such as sevoflurane, isoflurane, or nitrous oxide) will not be used.

**Fig. 2 fig2:**
[figure not shown]
Details of study interventions.

### Outcomes

2.6

For this noninferiority trial, the primary outcome is the cumulative time with EEG burst suppression, which is obtained from the SedLine system [26]. In addition, we will present the adjusted time with burst suppression (time spent in EEG burst suppression divided by surgical time).

The secondary outcomes include (1) the POD occurrence within the first 5 days postoperatively and (2) duration of perioperative hypotension (a decrease in mean arterial pressure >30 % of baseline which requires interventions). POD will be assessed using the Confusion Assessment Method (CAM) or CAM-ICU at 8:00 and 20:00 in the first five postoperative days. The assessment is based on 4 features: acute onset of mental state fluctuation, inattention, disorganized thinking, and consciousness alterations [27]. Patients presenting both features 1 and 2 with either feature 3 or 4 will be diagnosed as delirious [28,29].

Exploratory outcomes include time with PSI <25, time with SEF <8, intraoperative awareness, perioperative use of vasopressors and inotropes, postoperative complications (including myocardial infarction, heart block, new-onset of atrial fibrillation, respiratory failure, pneumonia, stroke, coma, acute kidney injury, renal replacement therapy, and surgical site infection), postoperative nausea and vomiting, reoperation, mechanical ventilation, duration of stay in ICU, length of postoperative hospital stay, 30-d readmission, and 30-d mortality.

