### Data management

2.7

We will collect the demographic data (age, gender, body mass index, smoking status, and education years), baseline data (ASA physical status, comorbidities, preoperative medications, and MMSE score), and perioperative data (surgical type, dose of anesthetics and analgesics, anesthesia time, surgical time, duration of CPB, transfusions). EEG information (left and right SEF, PSI, and burst suppression) will be recorded in SedLine and then data will be analyzed offline. Trained investigators will assess the occurrence of POD using the CAM-ICU or CAM postoperatively. All data will be de-identified and then registered on the web-based database (https://www.91trial.com). A data monitoring committee independent of the study team will conduct an ongoing review of study implementation.

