### Sample size

2.8

According to our institutional pilot data, the mean ± standard deviation (SD) time with EEG burst suppression was 10 ± 5.5 min in elderly patients who received cardiac surgery and propofol anesthesia. We set a noninferiority margin of 2 min based on clinical expert advice. To test the noninferiority of remimazolam with α = 0.025 and power = 80 %, 240 patients are required (n = 120 in each group). We consider a loss to follow-up rate of 8 %, and the target recruitment is set at 260 elderly patients (n = 130 in each group). We calculated the sample size using PASS (version 11.0.7, NCSs, LLC).

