## Discussion

3

We will recruit a total of 260 elderly patients undergoing cardiac surgery in this randomized controlled noninferiority trial to assess remimazolam vs. propofol for anesthesia and postoperative sedation. The primary hypothesis is that remimazolam would be noninferior to propofol in terms of the cumulative time of EEG burst suppression. We also plan to investigate the impact of remimazolam on the POD occurrence and duration of hypotension in these patients.

Recent studies have shown the relationship between postoperative cognitive function and EEG burst suppression. The characteristic pattern of EEG burst suppression is isoelectric periods with high-frequency and large-amplitude waves, suggesting an excessive depth of anesthesia or low cerebral perfusion [30]. An observational study comprising 619 surgical patients with planned admission to ICU showed that intraoperative EEG suppression could predict POD [31]. This association was also observed in patients undergoing cardiac surgery [32,33]. However, a clinical trial showed that anesthesia administration by EEG guidance reduced the cumulative time with EEG suppression but did not decrease POD in elderly patients who had major surgery [34]. Therefore, more efforts are still required to determine whether the avoidance of EEG burst suppression reduces POD.

A previous study showed that the time with burst suppression was 10.9 ± 2.6 min in patients who received neurosurgical procedures and propofol anesthesia [35]. A recent study showed that for patients receiving sevoflurane anesthesia and major surgery, the median (IQR) time with EEG suppression was 7 (1–23) min in the guided group and 13 (2–58) min in the control group, accounting for 2.7 % and 4.9 % of total anesthesia time respectively. However, there is no report on the frequency or cumulative time of EEG burst suppression during remimazolam anesthesia. In our pilot observation, time with EEG burst suppression was 10 ± 5.5 min in cardiac surgical patients who received propofol anesthesia. In this randomized controlled noninferiority trial, we set a margin of 2 min to test the noninferiority of remimazolam.

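### The primary noninferiority comparison uses none of the baseline variables already collected, in a design with almost no power to spare; a minor point is the undefined window behind the supplementary ratio

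*Protocol article*

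**What the plan says.** The sample size rests on an unadjusted SD. Pilot "time with EEG burst suppression was 10 ± 5.5 min in elderly patients who received cardiac surgery and propofol anesthesia", the article states "We set a noninferiority margin of 2 min based on clinical expert advice", and it concludes: "To test the noninferiority of remimazolam with α = 0.025 and power = 80 %, 240 patients are required".

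The Statistical analysis section names the t-test, Mann-Whitney, chi-square and Fisher tests, with an odds ratio, mean difference or median difference and its 95% CI. Noninferiority is declared if the upper limit for burst suppression time lies below 2.0 min. No covariate is named. Age and ASA class appear there only as subgroup factors. The Randomization section describes 1:1 permuted blocks of 2 or 4 and states no stratification.

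The Data management section lists as collected "demographic data (age, gender, body mass index, smoking status, and education years), baseline data (ASA physical status, comorbidities, preoperative medications, and MMSE score". It puts surgical type, anesthesia time, surgical time and CPB duration under perioperative data.

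The only quantity called adjusted is in the Outcomes section: "we will present the adjusted time with burst suppression (time spent in EEG burst suppression divided by surgical time". On the recording, the Anesthesia section says that the SedLine "system will be applied to monitor intraoperative EEG continuously". It gives no start or stop. The Discussion cites suppression times from a sevoflurane study, "accounting for 2.7 % and 4.9 % of total anesthesia time respectively".

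**The concern.** If baseline variables predict burst suppression, leaving them out of the primary model leaves explainable variance in the standard error and widens the interval that must clear 2.0 min. The design is sized almost exactly at 80%, and the per-protocol set, in which the primary analysis is also run, may be smaller than 120 per arm. With no stratification stated, a chance imbalance in age or ASA class would also go uncorrected in the main estimate. The article itself names advanced age as a risk factor for delirium and selects age and ASA class for subgroup analyses, so it treats both as relevant.

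The ratio is a smaller matter. Its label may lead a reader to think that covariates were controlled. If suppression minutes are counted from induction, some of them fall outside a surgical-time denominator. The result could not then be read as a share of monitored time or set beside the cited 2.7% and 4.9%.

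**Working it through.** **Inputs.** From the Sample size section: margin 2 min, SD 5.5 min, one-sided α 0.025, power 80%, 120 per arm, 8% loss, 260 recruited. Assumed: a true difference of 0 (not stated, but it reproduces the stated number) and R², the share of outcome variance explained by baseline covariates (not given; shown from 0 to 0.30).

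**Step 1: reproduce the stated number.**

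n per arm = 2 · SD² · (1.960 + 0.842)² / margin² = 2 · 30.25 · 7.85 / 4 = 118.7, so 119 per arm (238 in all) by the normal approximation. With the noncentral t distribution, power is 79.8% at 119 and 80.1% at 120 per arm, which gives the stated 240. The figure reproduces.

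**Step 2: how much slack there is.** 260 × (1 − 0.08) = 239.2, so the planned loss leaves about 239 patients against the 240 required.

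**Step 3: effect of covariates at 120 per arm.** Residual SD = 5.5 · √(1 − R²); SE = residual SD · √(2/120); noncentrality = 2 / SE; CI half-width = 1.96 · SE. Power is from the noncentral t with 238 degrees of freedom. Taking away a few more degrees of freedom for covariates changes it by less than 0.1 percentage point.

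| Assumed R² | Residual SD (min) | SE (min) | 2 / SE | Power | CI half-width (min) |
|---|---|---|---|---|---|
| 0 | 5.50 | 0.710 | 2.82 | 80.1% | 1.39 |
| 0.05 | 5.36 | 0.692 | 2.89 | 82.1% | 1.36 |
| 0.10 | 5.22 | 0.674 | 2.97 | 84.1% | 1.32 |
| 0.20 | 4.92 | 0.635 | 3.15 | 88.0% | 1.24 |
| 0.30 | 4.60 | 0.594 | 3.37 | 91.8% | 1.16 |

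The normal approximation gives 80.4%, 82.4%, 84.4%, 88.3% and 92.0%, which is the same picture.

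**Step 4: the ratio.** With assumed durations of 240 min of surgery and 300 min of anesthesia, the pilot mean of 10 min is 10/240 = 4.2% of the first and 10/300 = 3.3% of the second, a factor of 300/240 = 1.25. This shows only how far the choice of denominator can move the figure. Neither duration is in the article.

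**The case against.** The strongest reply is that nothing here is an error. An unadjusted interval is valid under randomization, its error rate already allows for chance imbalance, and it is the analysis that the sample size assumes. Covariates may be named in a full protocol or SAP that is not shown. The gain depends on an R² that the documents do not supply. It is zero at R² = 0 and may be low here, because eligibility narrows the population (age 60 or over, MMSE above 23, ejection fraction at least 30%) and the drug is titrated in every patient to limit burst suppression. All of this stands, and it makes the point a recommendation for better precision. It does not remove the point, since the tests and effect measures that the article names are unadjusted and the variables are at hand.

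Two details also stand. Surgical type is listed as perioperative, so planned procedure qualifies as a covariate only if it is recorded before randomization. And a covariate-adjusted logistic model for delirium would move the odds ratio from marginal to conditional, so the recommendation here is confined to the primary mean difference.

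A reader might infer that the ratio is simply wrong because surgical time is not the EEG window. The documents do not support that. They call the EEG intraoperative and define neither end of the recording, and Table 1 appears to mark it under the during-surgery column. The study drug appears in that column too, and the drug includes an induction dose. A window from induction is therefore plausible, but it is not stated. The ratio is presented alongside the primary outcome, is defined identically in both arms, and plays no part in the noninferiority rule. The article does not say that it will be compared with the cited percentages.

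**Conclusion.** The primary comparison is valid as planned and correctly sized on its own assumptions, but it leaves available precision unused when power is 80.1% at 120 per arm. Adjustment would add about 2 percentage points of power at R² 0.05, 4 at 0.10 and 8 at 0.20, and at R² 0.20 it would shorten the CI half-width from 1.39 to 1.24 min. These figures assume a true difference of 0, an SD of 5.5 min and the R² shown. The gain may be small or nil. It would be wrong to read this as bias, invalidity or an inadequate sample size.

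The ratio is a minor clarification. Its denominator differs from that of the cited benchmark, its match to the recording cannot be judged, and its label misleads. It cannot change the trial's conclusion.

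**What to change.** **Primary analysis.** Estimate the mean difference and its 95% CI from a linear model with treatment and a few pre-randomization covariates, fixed before unblinding: age, ASA class, and planned procedure if it is recorded before randomization. Use robust or bootstrap standard errors. Apply the 2.0 min rule to the upper limit of that interval and report the unadjusted difference as a sensitivity analysis. Surgical, anesthesia and CPB times arise after randomization and should not be covariates.

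**Ratio.** State when EEG recording for the outcome starts and stops. Divide by EEG-monitored time, or by anesthesia time if it covers the same window, or else justify surgical time. Call the result the proportion of time in burst suppression.

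**Cost.** These are wording changes and the sample size stays as it is. Anesthesia time, age and ASA class are already collected; planned procedure may need a recorded pre-randomization entry. The change commits the primary analysis to a mean difference and gives up the median difference that the article now allows. If R² is near zero, the loss in degrees of freedom is negligible at this size.

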### Data management

2.7

We will collect the demographic data (age, gender, body mass index, smoking status, and education years), baseline data (ASA physical status, comorbidities, preoperative medications, and MMSE score), and perioperative data (surgical type, dose of anesthetics and analgesics, anesthesia time, surgical time, duration of CPB, transfusions). EEG information (left and right SEF, PSI, and burst suppression) will be recorded in SedLine and then data will be analyzed offline. Trained investigators will assess the occurrence of POD using the CAM-ICU or CAM postoperatively. All data will be de-identified and then registered on the web-based database (https://www.91trial.com). A data monitoring committee independent of the study team will conduct an ongoing review of study implementation.

